##### 8.4.3 Estimation of cost-effectiveness

The primary analysis will be based on six-month follow-up of the trial for the incremental cost per QALY. A second analysis will be conducted for a 24-month time horizon using the same methods as outlined in this manuscript. The results will be presented as point estimates of mean incremental costs, QALYs, and incremental cost per QALY. Measures of variance for these outcomes are likely to involve bootstrapping estimates of costs, QALYs, and incremental cost per QALY. Incremental cost-effectiveness data will be presented in terms of cost-effectiveness acceptability curves (CEACs).

Other forms of uncertainty, e.g. concerning the unit cost of a resource from the different centres, will be addressed using standard deterministic sensitivity analysis. Where feasible the results of the sensitivity analyses will also be presented as CEACs.

A secondary economic analysis will be presented. In this analysis the costs and consequences measured in terms of visual function and adverse events will be presented as a cost-consequence analysis. Where appropriate uncertainty will be explored using similar approaches to those outlines above.

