### 8. Analysis of the data

#### 8.1. Statistical analysis

The principal analysis will take place when six month data collection is complete. A subsequent analysis will be conducted once 24 months data is available. The statistical analysis will be based on all patients as randomised, irrespective of subsequent treatment received and, thus, will follow the intention to treat principle. Additionally, the primary analysis will be based upon available case data with no imputation of missing values. Sensitivity analyses, which impute extreme values will be performed for the primary outcome (visual acuity at 6 months) and for other visual function and quality of life secondary outcomes as appropriate. Statistical significance for the primary and secondary outcomes will be based on two-sided tests with 2P ≤ 0.05 taken as the criterion for statistical significance. The primary outcome of ETDRS visual acuity score at 6 months will be compared between the two groups (ILM peel and no ILM peel) using a generalised linear model to calculate the mean difference adjusted for the baseline score and minimisation covariates. The primary outcome will additionally be analysed according to the pre-specified subgroups (see Treatment Allocation section, minimisation criteria, above) by including corresponding interaction term(s) in the regression model. For these subgroup analyses, stricter criteria for statistical significance (2P ≤ 0.01) will be applied. Secondary outcomes, adverse events and re-operation rates will be analysed using generalised linear model with adjustment for minimisation covariates as appropriate. Analyses of health related quality of life measures (EQ-5D and VFQ-25) and secondary measures of visual function (contrast sensitivity, MN Reading speed and distance and near visual acuity) will be adjusted for the corresponding baseline score in addition to the minimisation variables.

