##### 8.4.2 Estimation of effectiveness

In the economic analysis effectiveness at 6 and 24 months will be measured in terms of quality adjusted life years (QALYs). QALYs will be estimated by the participants' responses to the EQ-5D questionnaire (administered at baseline, 6 and 24 months). The estimation of QALYs will take account of the mortality of study participants. Participants who die within the study follow-up will be assigned a zero utility weight from their death until the end of the study follow up. QALYs before death will be estimated using linear extrapolation between the QALY scores at baseline and all available EQ-5D scores up to death or the end of the study follow-up. The method of eliciting QALYs described is one commonly adopted in economic evaluation [21].

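### Section 8.4 names no baseline EQ-5D adjustment for incremental QALYs, although half the weight of the 6-month QALY is a pre-treatment value and section 8.1 adjusts EQ-5D itself

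*Protocol article*

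**What the plan says.** Three parts of the protocol article bear on this.

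- **How QALYs are built (section 8.4.2).** "QALYs will be estimated by the participants' responses to the EQ-5D questionnaire (administered at baseline, 6 and 24 months"). The scores are joined by a straight line: "QALYs before death will be estimated using linear extrapolation between the QALY scores at baseline and all available EQ-5D scores up to death".
- **What is reported (section 8.4.3).** "The primary analysis will be based on six-month follow-up of the trial for the incremental cost per QALY". Of the estimates: "The results will be presented as point estimates of mean incremental costs, QALYs, and incremental cost per QALY". Of uncertainty: "Measures of variance for these outcomes are likely to involve bootstrapping estimates of costs, QALYs, and incremental cost per QALY". Of the longer horizon: "A second analysis will be conducted for a 24-month time horizon using the same methods as outlined in this manuscript". No covariates are mentioned for costs or QALYs.
- **How EQ-5D is treated as an outcome (section 8.1).** Analyses of EQ-5D, VFQ-25 and the secondary visual function measures "will be adjusted for the corresponding baseline score in addition to the minimisation variables". QALYs are not on that list. Section 7 does count incremental cost per QALY as a secondary outcome. On a generous reading, the general section 8.1 rule for secondary outcomes therefore applies, but that rule brings in only the minimisation covariates, as appropriate, and not baseline EQ-5D.

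EQ-5D is not among the minimisation factors in section 3.

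**The concern.** With only two EQ-5D measurements inside the primary horizon, half of each participant's 6-month QALY is fixed before surgery. If incremental QALYs are the plain difference between arm means, any chance difference in baseline utility goes straight into the primary economic estimate.

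Two things are at stake:

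- The economic result could disagree with the trial's own baseline-adjusted EQ-5D result for no reason other than chance imbalance.
- Incremental QALYs are the denominator of the cost per QALY and are likely to be small over six months. Avoidable noise there makes the ratio unstable and can change its sign.

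**Working it through.** **Inputs from the article.** EQ-5D at baseline, 6 and 24 months with a linear path between them (section 8.4.2); horizons of 6 and 24 months (section 8.4.3); 64 per group (section 9). The article gives no figure for QALYs or for the EQ-5D SD.

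**Inputs assumed.** EQ-5D SD of 0.15 to 0.30, equal at baseline and 6 months; baseline-to-6-month correlation r of 0.3, 0.5 or 0.7; participants alive with both scores.

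**The plan's own figure.** A two-sided 5% t-test with effect size 0.5 and 80% power needs 63.8 per group, so 64 (power 80.1%). The figure of 64 reproduces and is used below. With 10% loss from 140, 126 remain, or 63 per arm, which hardly alters the results.

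**Step 1: weights, by the trapezoid rule in years.**
- 6 months: 0.5 x (U0 + U6)/2 = 0.25 U0 + 0.25 U6.
- 24 months: the second segment lasts 1.5 years and gives 0.75 to each end, so the QALY is 0.25 U0 + 1.00 U6 + 0.75 U24.

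**Step 2: direct weight of a baseline difference d.**
- 6 months: 0.25d, against 0.25d for a treatment effect d at 6 months. The ratio is 1:1.
- 24 months: 0.25d, against (1.00 + 0.75)d = 1.75d for an effect d sustained at both later visits. The ratio is 1:7.

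**Step 3: carry-over at 6 months.** Baseline differences partly persist, so with equal SDs the expected total shift is 0.25d(1 + r). For d = 0.05:
- r = 0: 0.0125
- r = 0.5: 0.0188
- r = 0.7: 0.0213

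A simulation with SD 0.2, r = 0.5 and no treatment effect gave a slope of 0.376, against 0.375 in theory. The mean QALY difference was about zero, so there is no bias on average.

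**Step 4: size of chance imbalance.** The SE of the baseline difference is SD x sqrt(2/64).
- SD 0.15: SE 0.0265. Direct 95% contribution 0.25 x 1.96 x 0.0265 = 0.013 QALY.
- SD 0.30: SE 0.0530. Direct 95% contribution 0.25 x 1.96 x 0.0530 = 0.026 QALY.

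For scale, a true utility gain of 0.05 at 6 months is worth 0.25 x 0.05 = 0.0125 QALY.

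**Step 5: precision at 6 months.** The unadjusted variance is proportional to 2 + 2r, and the variance after regression on baseline to 1 - r². Adjusted over unadjusted is (1 - r²)/(2 + 2r) = (1 - r)/2.

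| r | Variance ratio | Unadjusted SE / adjusted SE |
|---|---|---|
| 0.3 | 0.35 | 1.69 |
| 0.5 | 0.25 | 2.00 |
| 0.7 | 0.15 | 2.58 |

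**Step 6: consistency with section 8.1.** Once baseline EQ-5D is a covariate, the 0.25 U0 term is absorbed by it. The arm coefficient for the 6-month QALY is then 0.25 times the adjusted 6-month EQ-5D difference from the same covariates and participants. The clinical and economic results would agree by construction.

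**The case against.** The strongest reply is that the article is silent here. A reader might infer that the plan commits to an unadjusted analysis, and the text does not support that: nowhere are incremental QALYs called raw or simple differences. The sentence on point estimates would also fit a regression-adjusted mean difference, and the bootstrap wording is tentative. A fuller health-economic plan may settle the matter. This limits what can be said to *names no adjustment*. It does not remove the point: section 8.4 fixes how QALYs are built, how deaths are handled and what is reported, and section 8.1 lists the measures adjusted for baseline without listing QALYs. Read literally, the result is a difference in means.

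Other inferences go too far:

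- **That the estimate is biased.** Imbalance averages zero under the trial's allocation. The issue is a shift given the imbalance that happens to occur, and lost precision. An unadjusted bootstrap would be inefficient, not invalid.
- **That nothing restrains the imbalance.** Minimisation on visual acuity in both eyes may limit its vision-related part.
- **That baseline counts as much as a treatment effect throughout.** That is true only of the direct weight at 6 months.
- **That the acceptability curves are much too wide.** They also reflect cost variance, for which there is no figure.

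Section 8.4.2 also says extrapolation where interpolation is meant. The meaning is clear from context, so this is a clerical slip.

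**Conclusion.** The point holds as a free improvement, not as an error in the clinical analysis. It concerns the economic evaluation only; the primary visual acuity outcome is untouched.

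Followed as written, section 8.4 gives a primary 6-month QALY difference with half its weight on a pre-treatment value, while section 8.1 already applies the better rule to the same questionnaire. Under the assumptions above, chance imbalance alone can move the estimate by an amount equal to or larger than the value of a 0.05 utility gain, and the standard error is two or more times what it need be at correlations of 0.5 and above. The direct weight and the form of the variance ratio follow from the article's construction and equal SDs. The QALY amounts rest on the assumed EQ-5D SD, and the SE ratios on the assumed correlation. The precision ratios apply to the 6-month analysis and leave aside the small cost of estimating the covariate effects.

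**What to change.** State in section 8.4.3, or in the health-economic analysis plan, that:

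1. Incremental QALYs are estimated by regression on arm, baseline EQ-5D and the minimisation variables, as section 8.1 already does for EQ-5D.
2. The regression is refitted within each bootstrap resample, with each participant's costs and QALYs resampled together so that their correlation is kept.
3. These adjusted increments feed the cost per QALY and the acceptability curves at both 6 and 24 months.

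At the same time, correct extrapolation to interpolation in section 8.4.2.

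The cost is a sentence or two and a few lines of code. Baseline EQ-5D is already collected and is already needed to form the QALY, so adding it as a covariate loses no participant. If a fuller plan already specifies this, a cross-reference is enough.

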### 9. Sample size

It was estimated that sixty-four participants will be required in each group, assuming a common standard deviation of 12 ETDRS points in these two randomised groups, to detect a 6 ETDRS score difference (an effect size of 0.5) using a two sample two sided t-test at a 5% level of significance and 80% power (128 patients). This calculation was based on estimated mean post treatment EDTRS visual acuity scores and the corresponding SDs for each intervention arm from published studies of alternative interventions for macular hole surgery [22,23]. To allow for a loss to follow up of 10% we aim to recruit a total of 140 participants into the trial.

For the subgroup analysis of stage, if 70% of the participants are recruited with the more severe stage 3 macular holes, the study will have 80% power to detect an effect size of 0.6. If a common standard deviation of 12 points is assumed, there will be sufficient power to detect a mean difference of 7 EDTRS letters between the randomised groups.

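### The 80% power stated for the stage subgroup analysis is that of a within-stage-3 comparison at 5%, not of the planned treatment-by-stage interaction judged at 2P ≤ 0.01

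*Protocol article*

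**What the plan says.** Protocol article, section 8.1 (Statistical analysis), plans subgroup analyses of the primary outcome for the minimisation criteria. Section 3 (Treatment allocation) lists stage of the hole among these. The subgroup analyses are to be done "by including corresponding interaction term(s) in the regression model", and for them "stricter criteria for statistical significance (2P ≤ 0.01) will be applied".

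Section 9 (Sample size) gives the main calculation first. It finds that "sixty-four participants will be required in each group" for a target difference of 6 letters. The variability is fixed by "assuming a common standard deviation of 12 ETDRS points in these two randomised groups", and the number is worked out "using a two sample two sided t-test at a 5% level of significance and 80% power (128 patients". A second paragraph turns to stage as a subgroup. Its claim is that "the study will have 80% power to detect an effect size of 0.6", and the condition placed on that claim is "if 70% of the participants are recruited with the more severe stage 3 macular holes". In letters, with SD 12, the section then says that "there will be sufficient power to detect a mean difference of 7 EDTRS letters between the randomised groups". That paragraph states no significance level and does not mention an interaction.

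**The concern.** Section 9 attaches its power to the subgroup analysis of stage, and section 8.1 defines that analysis. The two differ in contrast (a difference between arms against a difference in effect between stages) and apparently in significance level (5% against 1%). Both differences make the planned test weaker than the stated 80% suggests.

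The question is a live one in this trial. The Background says that some surgeons peel in all cases while others reserve peeling for large or long-standing holes, and the footnote to Table 1 separates stages 2 and 3 by a hole diameter of 400 microns. The stage interaction is the analysis that bears on selective peeling by hole size. A reader who took the 80% as its power would give a non-significant result more weight than the design can support.

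**Working it through.** **Inputs from the protocol.** 128 analysed, 1:1 allocation, SD 12 (section 9); 70% stage 3 and so 30% stage 2 (section 9); interaction test at two-sided 0.01 (section 8.1). Per arm this gives 0.7 × 128 / 2 = 44.8 at stage 3 and 0.3 × 128 / 2 = 19.2 at stage 2. Powers are from the noncentral t, with the normal approximation in brackets.

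**1. The plan's main figure.** A two-sample t-test for 6/12 = 0.5 SD at two-sided 5% and 80% power needs 63.8, so 64 per group and 128 in all. It reproduces.

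**2. The plan's subgroup figure.** Compare the arms within stage 3 only. The standard error in SD units is √(2/44.8) = 0.211.
- At 5%: 0.6/0.211 = 2.84, and Φ(2.84 − 1.96) gives power 80.2% (81.1%). This is the stated 80%.
- 7 letters is 7/12 = 0.583 SD, with power 77.9% (78.8%) at 5%.

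Section 9 does not state this contrast and level outright. They are inferred: 5% is the only level in the section, the letters are described as a difference between randomised groups, and the other variants tried do not give 80%. A two-sample comparison split 70:30 gives 87% at 5% and 69% at 1%.

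**3. The same contrast at the planned level.** At 1%, Φ(2.84 − 2.576) gives power 58.3% (60.4%) for 0.6 SD. 80% power needs 0.736 SD, and 0.736 × 12 = 8.8 letters.

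**4. The planned interaction.** The standard error of the difference in effect between stages, in SD units, is √(2/44.8 + 2/19.2) = √(0.0446 + 0.1042) = 0.386. A between-stage difference of 0.6 SD gives 0.6/0.386 = 1.555.
- At 5%: power 33.9% (34.3%); 80% power needs 1.09 SD, about 13 letters.
- At 1%: Φ(1.555 − 2.576) gives power 14.9% (15.4%); 80% power needs 1.34 SD, about 16 letters.

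**5. Number analysed.** At 1% the interaction power for 0.6 SD is 14.6% with 126 analysed (10% lost from 140) and 16.6% with all 140.

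**6. Covariate adjustment.** The planned model adjusts for baseline score and minimisation covariates. The document gives no correlation, so the values below are assumptions. The standard error is multiplied by √(1 − r²).

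| Assumed r | √(1 − r²) | Interaction power for 0.6 SD at 1% | Difference detectable with 80% power at 1% |
|---|---|---|---|
| 0 | 1.000 | 15% | 16 letters |
| 0.3 | 0.954 | 17% | 15 letters |
| 0.5 | 0.866 | 21% | 14 letters |
| 0.7 | 0.714 | 33% | 11.5 letters |

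The within-stage-3 contrast at 1% is more sensitive to this assumption. By the normal approximation its power for 0.6 SD is 60%, 66%, 76% and 92% at r = 0, 0.3, 0.5 and 0.7.

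**The case against.** The strongest reply is that section 9 says what its 0.6 means: a difference between the randomised groups, given a 70% share of stage 3. On that reading the sum is right and nothing is claimed about an interaction. This stands in part. A reader might infer that the protocol claims 80% power for a 0.6 SD interaction when the truth is 15%. The document does not say that, and the 15% concerns a different quantity. The like-for-like change is from 80% to 58%, from the level alone. The reply does not make the two sections agree, because section 9 presents the figure as belonging to the subgroup analysis of stage, which section 8.1 defines as an interaction at 1%.

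A second reply is that the planned model is adjusted, while the SD of 12 appears to be an unadjusted SD of post-treatment scores. This also stands, so the 58%, 15% and 16-letter figures hold only without covariate gain. Strong adjustment could bring the within-stage-3 contrast at 1% to 80% or more. It does not bring the interaction near 80% for 0.6 SD at any correlation considered.

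Third, 7 letters against 0.6 × 12 = 7.2 might look like an arithmetic error. It is rounding: 7/12 = 0.583 rounds to 0.6.

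Finally, nothing in the protocol says that a non-significant interaction will be read as no effect modification, and the stricter level already signals caution. The risk lies in how a reader may use the 80%. Whether to label the subgroup results exploratory, or which interval to report, is a reporting choice that an article may leave to the full protocol or the analysis plan.

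**Conclusion.** The point holds as an inconsistency between sections 8.1 and 9. The 80% belongs to a peel versus no-peel comparison within stage 3 at 5%, whereas the planned analysis is a treatment-by-stage interaction at 2P ≤ 0.01. Its size rests on SD 12, 128 analysed, a 70:30 split and no covariate gain, and the contrast and level behind the 80% are inferred from the reproduction.

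The mismatch between the sections does not depend on the correlation, and neither does the interaction's low power for 0.6 SD over the range considered. The 58% for the within-stage-3 contrast does depend on it.

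Severity is should-fix. A reader might infer that the trial is too small or its main calculation wrong. The documents do not support that: the 64 per group reproduces, and the primary test and level are untouched.

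**What to change.** Restate the second paragraph of section 9 so that it:

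- labels the 0.6 SD figure (about 7 letters) as a comparison of the arms within stage 3 at two-sided 5%, or gives it at 1% instead (about 58% power for 0.6 SD; about 8.8 letters for 80% power, without covariate adjustment);
- says that this is not the power of the interaction test in section 8.1;
- gives the between-stage difference in effect that the interaction can detect with 80% power at 2P ≤ 0.01: about 16 letters unadjusted, and about 15, 14 and 11.5 letters at assumed baseline correlations of 0.3, 0.5 and 0.7. If the trial team has its own estimate of the correlation, it should be stated and used in place of these.

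The cost is wording only. The stated power becomes less favourable; recruitment, the primary analysis and the planned subgroup test stay as they are.

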### 10. Organisation

#### 10.1 Local organisation

Each collaborating centre will identify a ***clinical co-ordinator***. The responsibilities of this person will be to 1) establish the trial locally, 2) take responsibility for clinical aspects of the trial locally (for example, if any particular concerns emerge), 3) notify the Trial Office of any suspected unexpected serious adverse event which might be related to trial participation, 4) ensure masking of the optometrist and participant to the allocated surgery.

Each participating centre will appoint a ***study optometrist ***to co-ordinate the day-to-day aspects of the trial. The responsibilities of this person are 1) to conduct visual assessment of the participants involved in the trial, 2) telephone the Trial Office to obtain randomisation and allocate treatment for participants enrolled in the study, and to let the vitreo-retinal surgeon know about it before the surgery, 3) arrange follow-up appointments, 4) keep regular contact with the local clinical co-ordinator, with notification of any problem or unexpected development, 5) maintain regular contact with the Trial Office, 6) provide information about the trial to the participants, 7) ensure CRFs are completed and sent to the Trial Office, 8) ensure that enrolled participants will undergo macular hole surgery within 2 weeks from the baseline assessment, 9) be masked to the allocated treatment, and 10) clarify the situation when the Trial Office fails to make a contact with a local participant, getting in touch by phone or a visit, if necessary.

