### 3. Treatment allocation

The existing central randomisation service (fully automated telephone randomisation) in the Centre for Healthcare Randomised Trials (CHaRT), Health Services Research Unit at the University of Aberdeen, will be used to randomise participants. A minimisation algorithm (according to Taves, with p = 1)^20^, considering trial centre, distance visual acuity in the study eye and in the fellow eye (20/40–20/160; 20/200–20/500; <20/500), duration of the macular hole (= 1 year; > 1 year), lens status (phakic;aphakic;pseudophakic) and stage of the hole (Grade 2; Grade 3), as classified by the vitreo-retinal surgeon will be used.

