### 4. Masking of intervention and outcome assessment

Patients, optometrists obtaining data on visual function, photographers and the observer at the University of Aberdeen responsible for analysing the size and status of the hole will be masked with regards to the type of procedure performed to the participant and will remain masked throughout the study. Only the vitreo-retinal surgeon, for obvious reason, will not be masked to the type of surgery performed.

At enrolment potential participants will be informed that they will be unaware as to whether they had received internal limiting membrane peeling at the time of the macular hole surgery. The surgeons will know which type of procedure they have performed but they will not reveal this to participants. The only scenario in which the participant will be unmasked is if the macular hole is not closed following surgery. In this situation, the participant will be offered further surgery and the nature of this surgery will be discussed with the participant.

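### As written, the optometrist who measures the primary outcome obtains and relays each allocation yet must be masked, and the article does not reconcile the two

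*Protocol article*

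**What the plan says.** Section 10.1 (Local organisation) lists ten duties for one study optometrist at each centre. Three matter here:

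- Item 1: "to conduct visual assessment of the participants involved in the trial".
- Item 2: "telephone the Trial Office to obtain randomisation and allocate treatment for participants enrolled in the study", and then "to let the vitreo-retinal surgeon know about it before the surgery".
- Item 9: "be masked to the allocated treatment".

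The same section makes the clinical co-ordinator responsible for masking; the fourth duty of that role is to "ensure masking of the optometrist and participant to the allocated surgery".

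Section 4 (Masking of intervention and outcome assessment) lists those who stay masked throughout: "Patients, optometrists obtaining data on visual function, photographers and the observer at the University of Aberdeen". It then names a single exception: "Only the vitreo-retinal surgeon, for obvious reason, will not be masked to the type of surgery performed".

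Section 3 (Treatment allocation) describes the service as "fully automated telephone randomisation". It does not say what the caller hears.

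Section 7 makes the ETDRS distance acuity score at 6 months the primary outcome. Table 1 shows near acuity, contrast sensitivity and reading speed among the other measures of visual function.

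**The concern.** Someone who obtains an allocation by telephone and passes it to the surgeon would ordinarily know it. Item 2 therefore conflicts with item 9 of the same list, with the co-ordinator's masking duty and with section 4. The article states both who makes the call and that this person is masked, so this is a conflict between two statements and not a detail left out for brevity.

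At stake is the masked assessment of the primary outcome and of the other visual measures taken by the optometrist. The article itself treats this masking as important. Sections 1.4, 2, 4 and 10.1 all mention it, and the surgical form is kept apart partly to protect it. A site that follows item 2 literally would defeat that protection for its own assessor. Because the duty is written for every participating centre, it could reach all 140 planned participants.

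**Working it through.** **1. The sections side by side**

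| Question | Answer in the article | Where |
|---|---|---|
| Who measures visual function? | Study optometrist | 10.1, item 1 |
| Who telephones for the allocation? | Study optometrist | 10.1, item 2 |
| Who tells the surgeon? | Study optometrist | 10.1, item 2 |
| Is the study optometrist masked? | Yes | 10.1, item 9; co-ordinator's duty 4; section 4 |
| Who is unmasked? | Only the surgeon | Section 4 |
| Does the service give a code, or release the allocation direct to the surgeon? | Not described | Section 3 |

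Item 2 taken literally and item 9 cannot both be met. They are compatible only if the caller never learns the arm, and no section says so. The separate handling of the surgical form (sections 1.4 and 2) covers what is written down at the operation. It does not cover a telephone call made before it.

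**2. What is exposed and what is not**

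- Baseline distance acuity is a minimisation factor (section 3), so it has to be known before the call. The exposure is to follow-up measurements, including the primary outcome.
- Participants do not learn their arm through item 2.
- Hole size and status are also read from photographs by a masked observer in Aberdeen, who has no part in the call.

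**3. The plan's own figure**

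Inputs from section 9: difference 6 letters, SD 12, two-sided 5%, power 80%.

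- Normal approximation: n = 2 × (1.96 + 0.8416)² / (6/12)² = 2 × 7.849 / 0.25 = 62.8, so 63 per arm.
- Two-sample t-test: 63.77, so 64 per arm, with power 80.1%.

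The stated 64 per arm reproduces, and this point does not change it.

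**4. Illustration of sensitivity to assessor bias**

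The bias values b below are assumptions; the article gives none. Take 64 per arm, SD 12, no true effect, and an average bias of b letters towards one arm.

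- SE = 12 × √(2/64) = 2.12 letters.
- Type I error = P(Z > 1.96 − b/SE) + P(Z < −1.96 − b/SE).

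| Assumed bias b | b/SE | Type I error | Share of the 6-letter target |
|---|---|---|---|
| 1 letter | 0.47 | 7.6% | 17% |
| 2 letters | 0.94 | 15.6% | 33% |
| 3 letters | 1.41 | 29.3% | 50% |

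The SE is for an unadjusted comparison. Section 8.1 plans adjustment for baseline score and minimisation covariates. If that reduces the SE, the same bias would inflate the error by more. The article gives no correlation from which to compute this.

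**The case against.** The strongest reply is that the article states the masking of the optometrist repeatedly and undermines it in only one clause. It does not say what the automated service reveals. A coded result, or a release straight to the surgeon, could sit in the full protocol or in the Site File mentioned under Publication. This reply stands in part. A reader might infer that assessors in this trial were in fact unmasked, and the article does not show that. It shows duties that conflict as printed, and the plain sense of allocating treatment and informing the surgeon is that the caller knows the arm.

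Three other strong readings are tempting and should not be drawn:

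- **That the locked surgical form serves no purpose.** Sections 1.4 and 2 say it protects participants as well as optometrists, and that protection remains.
- **That allocation concealment fails.** Concealment concerns knowledge before assignment. Assignment here is central and automated, and the surgeon has to know the arm before operating in any case. Knowledge after assignment is a matter of masking.
- **That a bias of 1 to 3 letters is to be expected.** Nothing in the article supports any particular value.

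It is also fair to say that masked participants and the masked photograph reading limit the damage. They do not protect the acuity score from an assessor who knows the arm.

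**Conclusion.** The contradiction is real, and the article does not resolve it. Section 10.1 gives the assessor of the primary outcome a task that, as printed, reveals the allocation, while the same section and section 4 require that assessor to be masked. If item 2 is followed literally, the 6-month ETDRS score and the other optometrist-measured visual outcomes are collected unmasked at every centre that does so.

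Confidence is high for the contradiction and lower for its consequence, which depends on what the service tells the caller and on what the sites do. The type I error figures of 7.6%, 15.6% and 29.3% rest on assumed biases, no true effect, SD 12, 64 per arm and an unadjusted analysis. They show how sensitive the trial would be to such a bias and do not estimate its size. The point must be fixed because it bears on the primary outcome and the remedy is cheap.

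**What to change.** 1. Remove the randomisation call and the relay of the allocation from anyone who measures visual function. The optometrist should supply only the baseline values needed for minimisation.
2. Have the automated service release the allocation directly to the surgeon, who is already unmasked, or to existing site or Trial Office staff with no part in visual assessment.
3. Reconcile sections 4 and 10.1. If a staff member other than the surgeon will learn the allocation, section 4 should name that role as unmasked too.
4. If a coded or direct release is already in use, state it where the call is described and reword item 2 to match.
5. If optometrists have already received allocations, record for which participants, and do not report the primary outcome assessment as masked for them.

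Moving randomisation into theatre, after the surgeon has confirmed that the vitreous is attached, is not part of this fix. It would change who is randomised and is a separate design decision.

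The cost is revised wording in the protocol and site documents and a short briefing to the eight sites. The minimisation factors, sample size and planned analysis do not change. Sites should confirm that existing staff can take the call.
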